## Abstract

**Introduction:**

Cancer is a leading cause of death worldwide. Early detection of cancer improves treatment options and patient survival but detecting cancer at the earliest stage presents challenges. Identification of circulating protein biomarkers for cancer risk stratification and early detection is an attractive avenue for potentially minimally invasive screening and early detection methods. This research aims to identify protein level changes that are downstream of genetic liability to lung cancer and colorectal cancer.

**Methods and analysis:**

PRS will be calculated using the PRS continuous shrinkage approach (PRS-CS and PRS-CSx) for colorectal and lung cancer risk. This methodology utilises effect sizes from summary statistics from genome-wide association studies (GWAS) available for the cancers of interest to generate weights via the continuous shrinkage approach which incorporates the strengths of the GWAS associations into the shrinkage applied. This methodology both improves upon previous PRS methods in accuracy as well as improving cross-ancestry application in the PRS-CSx approach. GWAS summary statistics will be from the Genetics and Epidemiology of Colorectal Cancer Consortium (GECCO) and the International Lung Cancer Consortium (ILCCO). The association between the polygenic risk scores and 2923 proteins measured by the Olink platform in UK Biobank (UKB) participants with protein measures available will be assessed using linear regression under the assumption of linearity in the proteomic data. The proteins identified could represent several different scenarios of association such as forward causation (protein causes cancer), reverse causation (cancer genetic liability causes protein level change), or horizontal pleiotropy bias (no causal relationship exists between the protein and cancer). Forward and reverse Mendelian randomization sensitivity analyses, as well as colocalization analysis, will be performed in efforts to distinguish between these three scenarios. Protein changes identified as causally downstream of genetic liability to cancer could reflect processes occurring prior to, or after, cancer onset. Due to individuals in the UKB having proteins measures at only one timepoint, and because UKB contains a mix of incident and prevalent cases, some protein measures will have been made prior to a cancer diagnosis while others will have been made after a cancer diagnosis. We will explore the strength of association in relation to the time between protein measurement and prevalent or incident cancer diagnosis.

## Introduction

Detecting cancer at an early stage is important because patients diagnosed early have a greater chance of being treated with curative intent and so experience increased long-term survival. Cancer is a leading cause of death worldwide [1] with survival rates considerably lower when diagnosis is made at a later stage. For colorectal cancer and lung cancer the 5-year survival is reduced from more than 9 in 10 and 6 in 10, respectively, when diagnosed at stage 1, to 1 in 10 for colorectal cancer and less than 1 in 10 for lung cancer when diagnosed at stage 4 [2]. The NHS Long Term Plan aims to increase early detection of cancers from half to three quarters by the year 2028 to improve cancer survival [3] as currently in England only 54% of cancers are detected early [4]. To meet this goal a number of research challenges need to be addressed, including development of methods for determining cancer risk (i.e., risk stratification) and identifying biomarkers which are effective for detecting cancer at an early stage [5].

One of the challenges to be overcome in improving cancer early detection is the identification of specific biomarkers for the cancers of interest that can be measured by minimally invasive, low-cost methods and are able to be implemented in a clinical setting. One way to address this challenge is the measurement of circulating protein levels in blood serum or plasma, potentially feasible because of the widespread use of blood tests in healthcare. Circulating protein biomarkers are a potentially useful tool for several clinical areas including identifying groups at high risk of the future development of cancer (risk stratification), early detection, disease diagnosis and monitoring biological processes [6,7]. They may provide a minimally invasive means of screening asymptomatic individuals for undiagnosed disease or for diagnosis of symptomatic patients [8,9]. An advantage of measuring protein within the blood is the reduced volume of sample required for analysis and affordability, as opposed to other minimally invasive methods, such as circulating-tumour DNA (ctDNA) sequencing. For the Olink explore 3072 panel, only 6 μL of plasma or serum is required vs. 4-5mL of plasma to obtain 5–10ng/mL of ctDNA and with the possibility of implementation of protein testing via ELISA, costing around ~£4 per test [10–15].

One approach to biomarker discovery is via prospective cohort studies to identify proteins associated with the incidence of a disease of interest, by measuring protein levels in individuals before diagnosis. These methods require large sample sizes over long periods of time to capture these events, at great financial and time cost [16]. A comparatively inexpensive technique for biomarker discovery has been formalised by Holmes and Davey Smith [17], and involves application of Mendelian randomization (MR) of disease liability as the exposure on protein levels as the outcome (sometimes described as reverse MR or reverse gear MR). Building on this idea, we propose that protein level changes resulting from cancer onset can be identified via an individual’s PRS for specific cancers, representing their genetic liability to developing that cancer. Defining the point of “cancer onset” remains difficult, with many possible mechanisms of initiation; for the purpose of this study we will use date of diagnosis to determine prevalent vs. incident cases within the cohort [18].

Proteins associated with genetic liability to cancer could reflect different mechanisms of association. Associations could reflect ‘forward causation’ where the protein is upstream of and causal for cancer, e.g., P1-6 (Fig 1, panel A) or ‘reverse causation’ where carcinogenesis is causing the change in downstream protein level, e.g., P7-9 (Fig 1, panel A). Proteins that are associated via forward causation are upstream of the cancer pathway and therefore do not always denote the presence of cancer but could identify potential therapeutic targets for cancer prevention and cancer prediction, these protein levels will likely remain stable over long periods of time. Proteins downstream of cancer development will likely show more variation in levels resulting from the progression of cancer; we will refer to these proteins as “reverse causal”. For proteins that cause cancer, most of the variants in the cancer PRS will have no causal relationship to those proteins, e.g., G9 and P6 (Fig 1, panel B), whereas for proteins that are causally associated downstream of cancer liability pathways, all variants in the PRS could contribute to the association signal (Fig 1, panel C). We thus expect a cancer PRS to be better powered for discovery of proteins downstream of cancer development. However, the relative balance in findings reflecting scenarios one (‘forward causation’) and two (‘reverse causation’) is likely to depend on the prevalence of cancer, including early or pre-clinical stages, in the sample used to measure the proteins. In general, the higher the prevalence, the greater the number of associations we expect to see reflecting effects of cancer liability pathways on protein concentration. Association of proteins with a genetic liability to cancer can also be due to factors other than genetic liability such as horizontal pleiotropy bias, as illustrated in Fig 1, panel A by G4 and G6; which may negate its use in risk stratification or early detection.

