## Methods and analysis

### Polygenic risk score analyses

PRS can be developed using GWAS summary statistics on the associations of many SNPs across the genome with cancer. In this way millions of SNPs can be combined to develop an individual’s PRS for a cancer. A PRS is the sum of the number of copies of risk alleles individuals have for SNPs across the genome, weighted by the effect size of these SNPs in relation to the disease of interest, in this case, cancer [19]. While the initiation of cancer and the factors that contribute to the onset and progression of cancer are still not fully understood [20]; by calculating a PRS using data from all SNPs across the genome, SNPs involved in initiation, promotion and progression of cancer will be captured by this score, reflecting the complex process of cancer development [18].

In this study, PRS will be calculated for UKB participants (Application ID: 15825/81499) with proteomic measurements (N = 49,542), individuals with sex-mismatch (derived by comparing genetic sex and reported sex) or individuals with sex-chromosome aneuploidy will be excluded from the analysis (N = 814) as well as highly related individuals related to a 3^rd^ degree to >200 individuals (N = 2) [21]. For colorectal cancer, we will use effect weights derived from GWAS summary statistics of the: i) Genetics and Epidemiology of Colorectal Cancer Consortium (GECCO) (GWAS Catalog Accession: GCST90255675) for Europeans; and ii) the Asia Colorectal Cancer Consortium (ACCC)/Korean-National Cancer Centre CRC Study 2 (Korea-NCC2) for GWAS summary statistics for East Asians. For lung cancer, we will use effect weights derived from GWAS summary statistics from the International Lung Cancer Consortium (ILCCO) (GWAS Catalog Accession: GCST004748). Sample selection and quality control within these studies has been previously described [22,23].

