### Olink proteins

Olink protein measurements were performed as part of the Pharma Proteomic Project (UKB-PPP) on blood plasma samples using the antibody-based protein Olink Explore 3072 Proximity Extension Assay. Proteomics were generated for 54,219 participants who were considered to be highly representative of the UK Biobank population on baseline characteristics and showed enrichment for selected diseases [30]. The number of participants with colorectal and lung cancers can be seen in Table 1. Quality control, sample selection and data processing has been described previously [30]. Associations between the participants’ PRS and 2923 Olink protein measures from the UK Biobank will be tested via linear regression, adjusting for age, sex, principal components and sample storage time where this has an impact on protein level variation [31]. Protein measures will undergo inverse rank normal transformation (INT) for each protein [32]. The number of independent proteins will be calculated using the metaboprep R package [33]. False discovery rate correction will be applied to p-values, proteins with p-value less than the calculated alpha will be prioritised for further analyses.

**Table 1 pone.0312970.t001:** Cancer frequency within the UKB cohort and within the UKB-PPP study participants.

ICD10/ICD9 code	Cancer	Number of cases (UKB)	Number of cases (UKB-PPP)
C18/153	Malignant neoplasm of colon	6015 (1.2%)	630 (0.13%)
C19/1540	Malignant neoplasm of rectosigmoid junction	642 (0.13%)	67 (0.013%)
C20/1541	Malignant neoplasm of rectum	2670 (0.53%)	268 (0.053%)
C34/162	Malignant neoplasm of bronchus and lung	5305 (1.1%)	597 (0.12%)
**ICD-O-3 Code**	**Histological Subset**	**Number of cases (UKB)**	**Number of cases (UKB-PPP)**
8140, 8211, 8250–8260, 8310, 8323, 8480–8490, 8550	Lung adenocarcinoma	2390 (0.48%)	261 (0.052%)
8070-8072	Lung squamous cell carcinoma	1244 (0.25%)	151 (0.03%)
8041–8042	Lung small cell carcinoma	502 (0.1%)	64 (0.013%)

Number of cases for each cancer type derived from UK Biobank phenotypic data with percentage of cases out of overall individuals is represented in brackets. UKB overall n = 501939, UKB with protein measures (UKB-PPP) n = 52996.

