### Further analyses

#### “Time-to” and “Time-from” diagnosis.

In observational analyses, we will evaluate the magnitude of the relationship between proteins, taken either pre or post-diagnosis, and cancer risk. This will involve an analysis of prevalent and incident cancer cases in UKB (Table 2) and a time variable derived from date of cancer diagnosis and time of blood collection [62,63]. To adjust for any variation in protein concentration as a result of sample storage and protein degradation over time [31], the relationship between storage time and protein level for all protein measures available will be assessed. Proteins are more likely to be causally downstream of cancer onset if the association with cancer is sensitive to time between protein measure and cancer diagnosis, a potential route for differentiating between normal baseline levels and levels that suggest the presence of cancer. If protein levels are detectable prior to patient reported symptoms proteins may be more suited for screening and early detection.

**Table 2 pone.0312970.t002:** Prevalent and incident cases of cancer from UKB cohort and within the UKB-PPP study participants.

ICD10/ICD9 Code	Cancer	UKB Overall		UKB-PPP	
		Prevalent Cases	Incident Cases	Prevalent Cases	Incident Cases
C18/153	Malignant neoplasm of colon	1029	4986	97	533
C19/1540	Malignant neoplasm of rectosigmoid junction	186	456	22	45
C20/1541	Malignant neoplasm of rectum	574	2096	60	208
C34/162	Malignant neoplasm of bronchus and lung	245	5060	31	566
**ICD-O-3 Code**	**Histological Subset**	**Prevalent Cases**	**Incident Cases**	**Prevalent Cases**	**Incident Cases**
8140, 8211, 8250–8260, 8310, 8323, 8480–8490, 8550	Lung adenocarcinoma	77	2313	8	253
8070-8072	Lung squamous cell carcinoma	74	1170	14	137
8041–8042	Lung small cell carcinoma	23	479	3	61

Number of incident and prevalent cases for each cancer type derived from UK biobank phenotypic data.

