### Strengths and limitations of this study

Strengths of the study:A strength of using PRS in the discovery step of identifying proteins to carry through into MR, is that lifetime genetic liability to cancer is captured with the use of a continuous measure of genetic risk. In contrast, using cancer registry data only captures those who already have a diagnosis and not those who may go on to be diagnosed imminently.This study will use a novel approach to construct PRS using weights generated from SNPs across the genome, we expect this to be more powerful for discovery in comparison with a PRS constructed using only genome-wide significant SNPs.Limitations of the studyLack of protein data for diverse population groups within available datasets; therefore, results may not be generalisable to ancestries outside of the European population for whom sufficient protein data was available for this study.UKB participants reflect a subset of the population that volunteered for the study, participants are from a higher socioeconomic position than average which could introduce collider bias.Prevalent cancer cases will reflect a specific subset of the general population with cancer, individuals who have survived cancer and were able to volunteer for the study; potentially introducing survivorship bias.It cannot be ruled out that proteins may reflect effects of processes beyond cancer liability to protein pathways.Lack of staging information for cancer cases within the UKB limiting our ability to distinguish early versus more advanced cancers.The proteomic technology currently used measures protein binding as opposed to protein levelsSubgroup analyses are more prone to false positive results which will require replication analysis to ensure these reflect actual associations.Power calculations have not been performed to assess the power of the subgroup analyses.

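### At the plan's own case counts the PRS-protein scan has little power for protein changes caused by cancer onset, so the Introduction's power expectation should be limited to liability-pathway effects

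*Protocol article*

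**What the plan says.** The Introduction proposes that "protein level changes resulting from cancer onset can be identified via an" individual's PRS. It reasons that every variant in the score may contribute to the signal for a downstream protein but only a few to that for an upstream one, and concludes: "We thus expect a cancer PRS to be better powered for discovery of proteins downstream of cancer development". The same paragraph then says that the balance of forward and reverse findings will depend on how common cancer, including pre-clinical cancer, is in the protein sample. It puts no number on this.

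The scan is fixed under Polygenic risk score analyses and Olink proteins: "PRS will be calculated for UKB participants (Application ID: 15825/81499) with proteomic measurements (N = 49,542"), and "2923 Olink protein measures from the UK Biobank will be tested via linear regression" with a false discovery rate correction whose level is not given. "Protein measures will undergo inverse rank normal transformation (INT) for each protein", so effects are in SD units.

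Case numbers are in Table 2 ("Prevalent and incident cases of cancer from UKB cohort and within the UKB-PPP study participants"), and the Table 1 note gives the denominators: "UKB overall n = 501939, UKB with protein measures (UKB-PPP) n = 52996". The document shows no power figure for the main scan. Strengths and limitations says only that none was calculated for the subgroups. That section also counts it in favour of the PRS that "using cancer registry data only captures those who already have a diagnosis and not those who may go on to be diagnosed imminently".

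**The concern.** The argument that all variants contribute leaves out a second factor. If a protein changes because a person has cancer, the PRS predicts that protein only as far as it predicts who has cancer, and few participants do. The signal is diluted by roughly the prevalence in the protein sample. The plan concedes that prevalence matters but does not apply this to its own counts.

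The scan is described as the discovery step, and proteins that pass it are prioritised for further analysis. Mendelian randomization (MR) and colocalization can help to reclassify a protein that passes, but cannot recover one that was never selected. If onset-driven proteins rarely pass, the scan will miss the kind of early-detection marker that the Introduction promises, and an empty result could be misread as absence of such markers.

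**Working it through.** **Inputs from the document**
- Scan size N = 49,542; proteins 2923; protein scale SD units.
- Colorectal cases with protein data (Table 2): prevalent 97 + 22 + 60 = 179; incident 533 + 45 + 208 = 786; total 965. Adding the three site rows assumes no one is counted twice.
- Lung: 31 prevalent + 566 incident = 597.
- Denominator 52,996; the same case fraction is assumed in the 49,542. Counts are used rather than the UKB-PPP percentages printed in Table 1, which divide by the whole cohort (630/501,939 = 0.13%, against 630/52,996 = 1.19%).

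**Assumptions not in the document**
- Odds ratio (OR) per SD of PRS: 1.5, range 1.2 to 2.0.
- Alpha: 0.05/2923 = 1.71e-5, two-sided, with 0.001 and 0.05 as lenient alternatives because the false discovery rate level is not stated.
- A step change of d SD in people with cancer, and no effect in others.

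The plan states no power figure, so there is none to reproduce.

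**Model.** The mean PRS differs between cases and non-cases by about ln(OR) SD. Hence slope ≈ d × p(1−p) × ln(OR), and expected z = √N × slope. A 400-run simulation at p = 1.8%, OR 1.5 and d = 1 gave a mean z of 1.61, matching the formula.

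**Slope needed.** SE = 1/√49,542 = 0.00449. For 80% power, (4.30 + 0.84) × 0.00449 = 0.0231.

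**Most favourable count: every recorded case already shifted at blood draw**

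| | Colorectal | Lung |
|---|---|---|
| p | 965/52,996 = 1.82% | 597/52,996 = 1.13% |
| p(1−p) | 0.01788 | 0.01114 |
| Dilution before the PRS effect, 1/[p(1−p)] | 56-fold | 90-fold |
| Slope for d = 1, OR 1.5 (× 0.4055) | 0.00725 | 0.00452 |
| Expected z | 1.61 | 1.01 |
| Shift for 80% power, OR 1.5 | 0.0231/0.00725 = 3.2 SD | 0.0231/0.00452 = 5.1 SD |
| Same, OR 2.0 to 1.2 | 1.9 to 7.1 SD | 3.0 to 11 SD |
| Power for d = 1 at 0.05/2923 | 0.4% | 0.05% |
| Power for d = 1 at 0.001 | 4.7% | 1.1% |
| Power for d = 1 at 0.05 | 36% | 17% |

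**What the rank transformation allows.** On a standard normal scale, a protein that separated cases perfectly would differ between cases and non-cases by φ(z_p)/[p(1−p)], where z_p cuts off the top fraction p. That is about 2.5 SD for colorectal and 2.7 SD for lung. At OR 1.5, the 3.2 and 5.1 SD above lie beyond what the planned scale can show.

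**Where power returns.** With OR 2.0, a 2 SD shift and every future case already shifted, power at 0.05/2923 is 89% for colorectal and 19% for lung.

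**A mechanism the model leaves out.** If a protein moves 0.15 SD per SD of liability in everyone, then at OR 1.5 (PRS-liability correlation 0.162) z = 0.15 × 0.162 × 222.6 = 5.4, and power is about 87%.

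**Direct comparison with the same data.** The detectable difference is 5.14 × √(1/cases + 1/non-cases): 0.18 SD with 786 incident colorectal cases and 0.22 SD with 566 incident lung cases.

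**The case against.** **The aim is wider than onset.** The Abstract and Aims speak of changes downstream of genetic liability, and the Abstract allows these to arise before or after onset. The step-change model sets liability effects in cancer-free people to zero, yet the scan may detect those well. This stands: the low power concerns onset effects only.

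**The plan admits that prevalence matters.** This stands too. The fault is that the dependence is never worked through, not that the plan is silent.

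**Prevalent counts are not cancer present at blood draw.** Using only the 179 and 31 prevalent cases gives required shifts of about 17 and 97 SD, which a reader might take as the headline. The plan defines prevalent by date of diagnosis; those people may have been treated, while undiagnosed disease sits among incident cases or goes unrecorded. The all-case figures are the fair ones.

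**Better powered is a relative claim.** A reader might infer that the true order is the reverse, with upstream proteins easier to find. The documents do not settle this. Assume protein heritability 0.2, liability heritability 0.15 and PRS OR 1.5. An upstream protein with OR 1.2 per SD has z = 3.5, against 1.6 for a 1 SD shift in all colorectal cases. At OR 1.1 the two are about equal (1.8 against 1.6), and with liability heritability 0.25 the upstream protein falls below (1.1).

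**Hits would be misread.** A reader might infer that every hit will be reported as caused by cancer. The plan lists forward causation, reverse causation, pleiotropy and population stratification as rival explanations, and specifies bidirectional MR, pleiotropy-robust methods and colocalization to separate them.

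**Onset proteins would be lost altogether.** The time-to-diagnosis section does not say that it is limited to proteins passing the scan. Whether it is gated is unclear, so exclusion is a risk rather than a stated rule.

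**Case comparisons have their own bias.** They carry confounding, and prevalent cases carry survivorship bias. The direct comparison above is a benchmark of power only.

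**Conclusion.** The point holds for protein changes caused by cancer onset. Even with every recorded case counted as shifted at sampling, 80% power at 0.05/2923 needs about 3.2 SD for colorectal and 5.1 SD for lung at an assumed OR of 1.5. At alpha 0.001 a 1 SD shift has about 5% and 1% power. The result rests on the assumed PRS odds ratio, the step-change model and the chosen thresholds. Among the combinations tried, only the corner with OR 2.0, a 2 SD shift and all future cases already shifted gives high power, and then for colorectal alone.

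The result does not show that the scan is uninformative: it can find proteins that respond to liability without cancer, upstream proteins and pleiotropic ones. Nor does it show which of upstream and downstream is better powered. The sentence on registry data is inaccurate for this dataset, because Table 2 already holds 786 colorectal and 566 lung cases diagnosed after sampling.

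**What to change.** 1. In the Introduction, limit the power expectation to effects of liability pathways, and state that at these case counts the scan has little power for changes caused by cancer onset. Put the calculation beside the sentence on prevalence.
2. Rerun each PRS-protein regression after removing prevalent and incident cases of that cancer. Do not attribute a hit to cancer onset if its slope is essentially unchanged.
3. State that the incident/prevalent comparison in the time-to-diagnosis section covers all 2923 proteins under its own false discovery rate, as a parallel discovery route not gated by the PRS result, with its confounding and survivorship limits noted.
4. Correct the registry sentence under Strengths and limitations to acknowledge the incident cases in Table 2.

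The cost is some wording, one repeat of the regressions and one wider case comparison, all on data already held. The claim for the PRS scan becomes less favourable.
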